**Results:**

The follow-up data collection started in August 2019 and the estimated end of data collection will be in May 2027. The study is still recruiting participants and 142 patients have been recruited as of November 2023. The DNA extraction and genotyping of the SNVs will be performed after inclusion of the last patient. Since no SNV genotypes have been determined, no data analysis has been performed to date. The results are expected to be published in 2027.

**Conclusions:**

This is the first prospective study of the *CD44* and *CHI3L2* SNV–based biomarker signature in PDAC. A prospective validation of this signature would enable its clinical use as a noninvasive predictive biomarker of survival after pancreatic resection that is readily available at the time of diagnosis and can assist in guiding PDAC therapy. The results of this study may help to individualize treatment decisions and potentially improve patient outcomes.

**International Registered Report Identifier (IRRID):**

DERR1-10.2196/54042

## Introduction

Pancreatic ductal adenocarcinoma (PDAC) is the most frequent type of pancreatic cancer and one of the most lethal malignancies due to a tendency for early local invasion and high metastatic potential [1,2]. Despite this aggressive phenotype, PDAC shows a wide range of biological features, whereby early recurrence is observed in some patients who undergo pancreatic resection, whereas long-term cancer-free survival can be achieved in others [3-5]. It is considered that such individual oncologic courses and the response to personalized treatment plans can be predicted by gaining a more comprehensive understanding of human germline genetic variation [6,7]. Importantly, this genetic information can be found in the germline DNA and thus does not require a tumor biopsy or the technically demanding isolation of circulating tumor cells. Instead, samples can be easily obtained by a simple and cheap blood or saliva test at any time during diagnostic workup or treatment, offering a noninvasive predictive biomarker available at the time of diagnosis. Indeed, this type of personalized medicine is no longer a fantasy but a maturing reality. In other cancer types, including acute lymphoblastic leukemia, colorectal cancer, lung cancer, and breast cancer, the genotyping of certain single-nucleotide variations (SNVs; formerly SNPs) is recommended by the US Food and Drug Administration [8].

A growing body of evidence suggests that inherited genetic variants can also be used to predict cancer-specific patient outcomes and guide therapy for patients with pancreatic cancer. Specifically, in a retrospective analysis, we identified a germline variant in the CD44 gene (rs187115) that can serve as a predictive biomarker to help select patients who are likely to benefit from pancreatic resection [9,10]. More recently, we performed a genome-wide screen for inherited variants that affect survival in patients with PDAC based on existing biological knowledge about the regions where the genetic variants reside [11]. This search for high-frequency polymorphic variants that affect tumor-related survival and either result in an altered protein structure and function or reside in known regulatory noncoding genomic regions has identified two clinically relevant sequence variants in functional regions of genes that are known to regulate cancer progression, invasion, and metastasis [11]. Specifically, regulatory variants within *CHI3L2* (rs684559) and *CD44* (rs353630) were found to be associated with an over 2-fold increased risk of tumor-related death in two independent retrospective PDAC study cohorts from Europe and the United States (hazard ratio [HR] 0.38, 95% CI 0.27-0.53; *P*=1×10^–8^, q value<.05) [11].

Taken together, these retrospective studies have demonstrated the potential of polymorphic sequence variants to identify a subset of patients with high-risk pancreatic cancer associated with a very low survival probability that might be eligible for inclusion in clinical trials of new therapeutic strategies, including neoadjuvant chemotherapy protocols and novel adjuvant systemic regimens. In addition, the findings from these studies suggest that the biological knowledge about these SNVs could help guide the development of such individualized genomic treatment strategies.

However, despite their robustness, the described results have not yet been validated prospectively and it is unclear whether these observations can be independently replicated in a controlled clinical setting.

## Methods

### Study Aim, Design, and Setting

This project is designed as a one-arm prospective controlled clinical study that aims to validate the association of the previously identified SNVs in the CD44 and CHI3L2 genes with PDAC survival after tumor resection. We aim to use a prospective cohort of patients with PDAC who will undergo pancreatic resection at our established network of three cantonal hospitals (Departments of Surgery at the Cantonal Hospital of Winterthur, Cantonal Hospital of Lucerne, and the Triemli Hospital in Zurich) in Switzerland. The study outline is depicted in Figure 1.

**Figure 1 figure1:**
[figure not shown]
Study outline. A planned sample of 150 consecutive patients with histopathologically confirmed resectable pancreatic ductal adenocarcinoma (PDAC) will be treated at three designated Swiss hospitals according to the best standard of care and prospectively included in the study. The first patient was included in August 2019 and the recruitment is ongoing. The estimated end of data collection is May 2027. The survival analysis using the single-nucleotide variation (SNV) genotyping data after DNA extraction from the blood collected at the time of inclusion will be performed after completion of the follow-up of all patients to ensure that all study participants and physicians are fully blinded with regard to the SNV genotypes of the patients. AJCC: American Joint Committee on Cancer.

### Participant Characteristics

Patients with a diagnosis of a pancreatic tumor mass that is either biopsy-proven or highly indicative of PDAC will be recruited before surgery in the outpatient clinics of the participating centers after completed standard preoperative evaluation of a pancreatic cancer diagnosis and assessment of tumor resectability according to the best standard of care and the following criteria: (1) pancreatic tumor mass either biopsy-proven or highly indicative (as assessed by preoperative magnetic resonance imaging, computed tomography, and/or endoscopic ultrasound imaging) of PDAC in the head or tail of the pancreas; (2) tumor, node, and metastasis stage c/uT1-4, c/uNx, cM0 (according to the 7th edition of the American Joint Committee on Cancer staging system); (3) open or minimally invasive pancreatic resection, including conversion laparotomy; (4) underwent primary tumor resection; (5) received neoadjuvant chemotherapy and/or radiochemotherapy; (6) previously underwent pancreatic resection for reasons other than PDAC; (7) age≥18 years; and (8) provided written informed consent. Patients who subsequently successfully undergo tumor resection and whose diagnosis of PDAC is confirmed by histopathological examination of the resected specimen will be included in the study. All patients who fulfill these criteria will be included, regardless of the tumor resection margins (R0, R1, R2) and regardless of intra- or postoperative mortality.

The presence of one of the following criteria will lead to the exclusion of the patient: (1) any histopathological entity other than PDAC, including but not limited to adenocarcinoma of the papilla of Vater, acinar cell carcinoma, distal cholangiocarcinoma, and neuroendocrine tumors such as neuroendocrine carcinoma; (2) metastatic disease, including intraoperative findings confirmed by histopathological examination (cM1, pM1); (3) previous pancreatic resection for PDAC and presenting either with local recurrence or a second primary tumor in the pancreatic remnant, but not yet included in the study; (4) age<18 years; and (5) did not provide written informed consent. With respect to exclusion criterion (3), individuals who had already been included in the study at the time of the first resection of a PDAC will not be excluded from the study retrospectively because of a local recurrence or a second primary tumor but will continue to receive follow-up. All patients that will be excluded from participation will be recorded together with the reason for the exclusion.

### Endpoints and Data Collection

The primary endpoint of the study is tumor-related survival. Secondary endpoints include recurrence and overall survival. The exact type and timing for data and blood sample collection are detailed in Table 1. The estimated total duration of the study is 5 years, including the scheduled 3-year postoperative follow-up.

**Table 1 table1:** Type and timing of data and blood sample collection.

Data and timing of collection	Screening	Surgery	Early postoperative period	Follow-up
Visit	1	2	3	4, 5, and 6
Time	Preoperative	day 0	1 week postoperative	1, 2, and 3 years
Participant information and informed consent	✓			
Medical history	✓			
Inclusion/exclusion criteria check	✓			
Blood collection	✓			
Surgical procedure		✓		
Histopathological data			✓	
Recurrence/survival data				✓

All cases will be presented at interdisciplinary tumor board meetings at each participating center pre- and postoperatively. All patients will be offered standard-of-care multimodal treatment at the discretion of the interdisciplinary tumor board at each participating center. The operation will be performed according to the group assignment by senior surgeons only, who have extensive experience in pancreatic resections. All surgeries will be performed at the Departments of Surgery at the Cantonal Hospital of Winterthur, Cantonal Hospital of Lucerne, and the Triemli Hospital in Zurich. The follow-up of the patient will be recorded for at least 3 years after tumor resection. Data collection will be completed using the hospital records or by contacting the patient’s general practitioner or oncologist; thus, no additional appointments in the outpatient clinic will be required for study purposes.

### Power of the Study

Sample size calculations were performed in G-Power 3.1 software (Heinrich-Heine University, Germany) based on the results of the previously mentioned retrospective studies according to the ability to detect an HR>2 between genotypes [9-11]. With the use of a two-sided α level of .05 and considering a dropout rate of 10% as well as a potential additional error margin of 10%, 150 patients are required to obtain 80% power to detect a difference in cancer-related survival between genotypes.

### Statistical Analysis

A parametric two-sided Student *t* test and a two-tailed Mann-Whitney *U* test will be used to compare data distributions in groups with normally distributed data and data that deviate from a normal distribution, respectively. The Fisher exact test will be used to calculate frequency distributions in cross-table analyses. Kaplan-Meier survival curves (log-rank test) and Cox proportional hazards models will be calculated to assess and compare survival times. All statistical analyses will be performed using R and SPSS software.

### Ethical Considerations

The study will be carried out in accordance with principles enunciated in the current version of the Declaration of Helsinki, the guidelines of Good Clinical Practice (GCP) issued by the International Council for Harmonisation of Technical Requirements for Pharmaceuticals for Human Use, and the requirements of the Swiss regulatory authority. The study was approved by the local ethics committee (Kantonale Ethikkommission Zürich, BASEC-Nr. 2019-00178) on April 18, 2019. All patients will be asked to sign a written informed consent form that has been approved by the ethics committee, which describes in detail the aims and methods of the study as well as lists all potential risks posed to the participants. Privacy and confidentiality are fully ensured since the study data are anonymous and deidentified. All data relevant to this study will be coded (including biological material and health-related personal data), safely protected, and recorded in a digital format using a GCP-compliant electronic data capture system. The study participants will receive no financial compensation for participating in the study.

## Results

The follow-up of the patients started in August 2019. The estimated end of data collection is May 2027. Recruitment is ongoing. As of November 2023, 142 patients have been recruited.

The DNA extraction and genotyping of the SNVs will be performed after the inclusion of the last patient. The data analysis will be performed at the end of follow-up of the last patient. Since no SNV genotypes have been determined, no data analysis has been possible to date. The results are expected to be published in 2027.

## Discussion

This is the first prospective study of the clinical value of *CD44* and *CHI3L2* SNV–based biomarkers in PDAC after tumor resection. The design of this study enables minimizing the biases inherent in retrospective trials, such as selection or publication biases. Moreover, akin to a randomized controlled trial designed to compare clinical interventions, both the study participants and all physicians involved in the treatment of the included patients will be fully blinded by determining the SNV genotypes and analyzing the results only after the completion of follow-up of all patients. Such a prospective validation of these biomarkers would allow for their clinical use as a predictive signature of survival after pancreatic resection that can be readily available at the time of PDAC diagnosis.

The main limitation of the study is the heterogeneity of the patient group with regard to the neoadjuvant and adjuvant treatment(s) the individual participants will receive. These treatments are known to affect patient outcomes, including cancer-related survival as the main endpoint of this study. However, this heterogeneity also reflects real-world clinical practice and should thus provide a robust biomarker that can be applied to all patients with PDAC who undergo resection of their tumors, regardless of the chemoradiotherapy they individually receive. Another limitation is the disruption of administrative and processes during the COVID-19 pandemic. However, since patients diagnosed with pancreatic cancer received adequate treatment without major delays and were included consecutively in this study during this disruptive period, the effect on the study results should be negligible.

The genotype of the identified SNVs can be determined before the start of any treatment by a technically simple blood or even saliva test, which can then be used to identify patients who are at higher risk for faster tumor progression [6,9]. Other prognostic factors currently in use or suggested to be useful in a clinical setting such as completeness of resection, lymph node involvement, or postoperative carbohydrate antigen 19-9 serum levels can only be precisely determined after surgical resection and therefore have limited relevance to treatment decisions [12]. In contrast, SNV-based biomarkers can guide preoperative treatment decisions such as the decision to perform neoadjuvant chemotherapy in patients with an aggressive tumor biology or can affect adjuvant treatment protocols. The results of this prospective study may lead to improved patient outcomes in patients with PDAC that is amenable to resection.

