**Methods:**

All patients with PDAC who will undergo pancreatic resection at three participating hospitals in Switzerland and fulfill the inclusion criteria will be included in the study consecutively. The SNV genotypes will be determined using standard genotyping techniques from patient blood samples. For each genotyped locus, log-rank and Cox multivariate regression tests will be performed, accounting for the relevant covariates American Joint Committee on Cancer stage and resection status. Clinical follow-up data will be collected for at least 3 years. Sample size calculation resulted in a required sample of 150 patients to sufficiently power the analysis.

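### The article claims the biomarker holds whatever treatment patients receive, but no described analysis tests this and the listed Cox covariates omit neoadjuvant treatment

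*Protocol article*

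**What the plan says.** Eligibility covers both primary resection and patients who "5) received neoadjuvant chemotherapy and/or radiochemotherapy" (Participant Characteristics). Treatment is not fixed: patients are offered "standard-of-care multimodal treatment at the discretion of the interdisciplinary tumor board at each participating center" (Endpoints and Data Collection).

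The Abstract (Methods) says that log-rank and Cox tests will be run for each locus, "accounting for the relevant covariates American Joint Committee on Cancer stage and resection status". The Statistical Analysis section adds only that "Kaplan-Meier survival curves (log-rank test) and Cox proportional hazards models will be calculated to assess and compare survival times". It names no covariate, stratum, subgroup or interaction.

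The Discussion says: "The main limitation of the study is the heterogeneity of the patient group with regard to the neoadjuvant and adjuvant treatment(s"). It goes on: "These treatments are known to affect patient outcomes, including cancer-related survival as the main endpoint of this study". It then argues that this heterogeneity "should thus provide a robust biomarker that can be applied to all patients with PDAC who undergo resection of their tumors", whatever chemoradiotherapy the individual received. The next paragraphs propose the marker as a guide to preoperative decisions, including whether to give neoadjuvant chemotherapy.

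**The concern.** Two things do not fit together.

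First, the article names a factor that it says drives the primary endpoint, then gives a list of relevant covariates without it. Leaving a strong prognostic factor out of a Cox model pulls the genotype HR toward 1 and costs some power.

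Second, the article treats heterogeneity as if it produced robustness. A mixed cohort yields an HR averaged over the mixture. That average can be well above 1 when the association is present in one treatment group and absent in another. Because the marker is meant to inform neoadjuvant decisions, whether its association with survival differs by neoadjuvant status is central to its use.

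**Working it through.** **Inputs from the article.** HR above 2 (taken as 2), two-sided alpha 0.05, 80% power, 150 patients, 10% dropout plus a 10% margin (Power of the Study); at least 3 years of follow-up (Endpoints and Data Collection). Removing both allowances leaves 150 × 0.9 × 0.9 = 121.5, so about 121 analysable patients.

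**Assumed, because the article does not give them.** Genotype split, neoadjuvant share, treatment effect, median survival and event proportion. Results are shown over a range.

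**1. The plan's own figure.** Events needed are (1.960 + 0.842)² / [q(1−q)(ln 2)²], with q the genotype share. This gives 66 at q = 0.5 and 78 at q = 0.3. With q = 0.3 and 65% events, 78/0.65 = 120 patients, and 120/0.81 or 120/0.8 gives 149 or 150. So 150 cannot be reproduced from the stated inputs alone, but plausible assumptions reach it. It is not shown to be wrong.

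**2. Cost of omitting treatment.** Simulated Cox models: n = 121, exponential survival, reference median 20 months, censoring at 36 months, genotype HR 2, q = 0.5 or 0.3, 30% or 50% neoadjuvant, treatment independent of genotype, 1000 runs per scenario. Ranges are over the four combinations of split and share.

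| Treatment HR | Genotype HR, omitted | Genotype HR, adjusted | Power, omitted | Power, adjusted | Loss (points) |
|---|---|---|---|---|---|
| 0.7 | 1.99-2.02 | 2.01-2.06 | 0.86-0.91 | 0.87-0.92 | 1-2 |
| 0.5 | 1.93-1.95 | 2.01-2.04 | 0.80-0.88 | 0.85-0.91 | 3-5 |
| 0.35 | 1.85-1.92 | 2.01-2.09 | 0.74-0.80 | 0.83-0.88 | 5-9 |

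A second simulation (n = 122, 35% carriers, baseline median 30 months, 3000 runs per scenario, stratified against unstratified Cox) agrees. An omitted factor with HR 2 in 30% of patients gives HR 1.93 against 2.01 and power 84.5% against 87.1%. HR 2.5 in 40% gives 1.87 against 2.02 and 82.3% against 88.2%. At HR 1.5 the loss is under 1 point. Neither simulation includes stage or resection status.

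**3. What a pooled HR can show.** With equal genotype splits, the pooled log HR is roughly the event-weighted mean of the stratum log HRs. Suppose 30% of events fall in a group where the genotype HR is 1. A pooled HR of 2 then needs ln 2 / 0.7 = 0.990 in the other group, an HR of 2.69. So a pooled HR of 2 fits both a uniform effect and no effect in 30% of the cohort.

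**4. Could an interaction test settle it?** SE of the log HR ratio = 1/√[D q(1−q) g(1−g)], with D events and g the neoadjuvant share.
- Least favourable case, D = 75, q = 0.2, g = 0.3: SE = 1/√(75 × 0.16 × 0.21) = 0.63. Power for a ratio of 2 is Φ(0.693/0.63 − 1.96), about 19%.
- Most favourable case, D = 121 (every analysable patient has an event), q = g = 0.5: SE = 1/√(121 × 0.0625) = 0.364. Power is about 48%.
- 80% power for a ratio of 2 needs 262-487 events. With 75-121 events the detectable ratio is about 2.8-5.8, so even the 2.69 contrast in step 3 would fall short of 80% power.

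**5. Precision within a stratum.** 30% of 122 is 37 patients, with about 27 events and 35% carriers. SE = 1/√(27 × 0.35 × 0.65) = 0.403, so a true HR of 2 has a 95% CI of exp(0.693 ± 1.96 × 0.403), about 0.9 to 4.4.

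**The case against.** The strongest reply is that little is lost. With a modest treatment effect the omission costs at most about 2 points, and power stays above the planned 80%. It falls below 80% only with a very strong effect (HR 0.35). The simulations also leave out stage and resection status, which the plan does adjust for and which could absorb part of the treatment effect. This stands: the gain over the actual planned model has not been computed.

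The marker is meant to be read before any treatment, so an HR averaged over later treatment is a legitimate target. This stands too, but it supports a statement about an average, not one about every treatment group. The planned model already conditions on stage and resection status, which are also determined after a germline genotype, so adding neoadjuvant status is no departure in kind.

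The authors disclose the limitation and hedge the conclusion, and a fuller plan may contain more. But the Abstract does state a covariate list, and the inference in the Discussion is faulty as written.

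A reader might infer more than the document supports:
- **Confounding.** The genotype is germline, and patients and physicians are blinded to it, so treatment cannot be chosen on the study's genotype results. No confounding is demonstrated.
- **A repaired stage coefficient.** Stage and margin may mean something different after neoadjuvant treatment, but stratifying by treatment still leaves one common stage coefficient. The article also does not say whether clinical or pathological stage is meant.
- **A need for hospital strata.** Nothing in this argument or its calculations concerns hospital.
- **Subgroup results that decide the matter.** Steps 4 and 5 show that they will be too imprecise.

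**Conclusion.** The point holds in two parts of unequal strength. The firm part needs no assumed figures: the article infers applicability across treatments from a pooled analysis that cannot show it, and describes no analysis that addresses it. The weaker part is the covariate omission. It conflicts with the article's own statement that treatment affects the primary endpoint, but its cost is conditional: about 0-2 power points with little attenuation if the treatment effect is modest, and about 3-9 points with an estimated genotype HR of about 1.85-1.95 if it is strong. Those ranges rest on assumed treatment shares and effects, genotype splits and median survival, and on models without stage or resection status. The primary test is not invalid, and the sample size is not shown to be wrong.

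**What to change.** Make these changes before genotypes are determined; the article reports that none had been.

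1. Add neoadjuvant treatment (yes/no) to the Cox model as a prespecified stratum or covariate, and stratify the log-rank test by it. First confirm that it is captured: Table 1 lists medical history at screening but no treatment field.
2. Report the genotype HR with 95% CI by neoadjuvant status, and the interaction estimate, as descriptive only. State that interaction power is about 19-48% for an HR ratio of 2.
3. Do not enter adjuvant therapy as a baseline covariate. It is given after surgery, and only to patients who survive and recover enough to receive it.
4. Reword the Discussion: the pooled HR is an average over the treatments received, and consistency across treatments will be described but not established.

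The cost is one degree of freedom and slightly more analysis work, with no new patients or visits. Made after genotyping, the same change would look data-driven.
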